## Abstract

**Background:**

Following successful treatment, displaced intra-articular calcaneal fractures (DIACFs) necessitate an extensive rehabilitation regimen, significantly influencing functional and socio-economic outcomes. Apart from surgical intervention, the implementation of a comprehensive rehabilitation protocol is crucial to optimize foot stability and functional recovery. The objective of this study is to ascertain the optimal rehabilitation protocol for patients with surgically treated DIACFs, either permissive weight bearing (PWB) or Restricted Weight Bearing, focusing on functional outcomes, health-related quality of life (HRQoL), radiographic parameters, cost-effectiveness, and incidence of complications.

**Methods:**

Study design: A prospective multicenter randomized controlled trial. Study population: Presence of surgically (extended lateral, sinus tarsi, or percutaneous approach) treated unilateral DIACFs (Sanders type II to IV), aged 18–67 years (labor force). Patients must be able to understand and follow weight bearing instructions. N = 115 patients with DIACFs will be included. Interventions: Patients with DIACFs will be randomly allocated to one of the rehabilitation protocols, either PWB or RWB. Primary outcome measure: Functional outcome, measured with the American Orthopaedic Foot & Ankle Society Score (AOFAS)). Secondary outcomes: Functional outcome (Maryland Foot Score, MFS), HRQoL (EuroQol-5D, EQ-5D), differences in radiographic parameters, cost-effectiveness, and complications. Nature and extent of burden: The PWB protocol is aimed to be non-inferior to the RWB protocol. Previous analysis of this protocol in other lower extremity fractures has shown a safe complication rate. Follow-up is standardized according to current trauma guidelines, namely at time points 2, 6, 12 weeks, and 6 months. The radiation exposure for both groups will differ from standard care (one extra CT scan of the foot will be made). Therefore, the burden for participants is considered minimal, with no significant health risks.

**Discussion:**

This study will be the first study to define an optimal rehabilitation regime for surgically treated patients with DIACFs. The limitations of this study include the absence of patient blinding, as this is impossible in rehabilitation. Additionally, the primary outcome measure (AOFAS) has limited validity for DIACFs. However, it is the most commonly used questionnaire in the literature on DIACFs. There is an apparent need since current literature is lacking on this specific topic.

**Trial registration:**

ClinicalTrials.gov NCT05721378, accepted on February 7, 2023.

**Supplementary Information:**

The online version contains supplementary material available at 10.1186/s13063-024-08617-5.

### Introduction

#### Background and rationale {6a}

Fractures of the calcaneus constitute up to 2% of all fractures and account for 60% of all fractures of the foot. Among calcaneal fractures, approximately 65% are intra-articular [1]. Surgical intervention is frequently required to restore the subtalar joint and the anatomical shape of the calcaneus. Given that calcaneal fractures predominantly affect middle-aged males, their socio-economic ramifications are considerable [2–5]. Approximately 20% of patients will not return to work within 1 year after injury [6]. Hence, post-fracture rehabilitation plays a pivotal role in the management of calcaneal fractures.

“The PermIssive Or Non wEight bEaRing in calcaneal fractures study” (the PIONEER study) will be the first prospective randomized controlled trial (RCT) comparing two rehabilitation protocols. Increasing evidence suggests that early weight bearing protocols such as permissive weight bearing (PWB), reduce the time to full weight bearing without adversely affecting patient-reported quality of life, pain levels, or complication rates [7, 8]. The greatest benefits of early weight bearing in lower extremity fractures are believed to be realized within the initial 6 months post-surgery [9]. Additionally, a recent systematic review on calcaneal fractures indicates that Early Weight Bearing (EWB) may not lead to inferior outcomes compared to the current, more conservative, weight bearing regimes [10]. Presently, both non-weight bearing (NWB) and EWB protocols are utilized in Dutch hospitals for calcaneal fractures [11]. However, a prospective study comparing these two rehabilitation protocols in displaced intra-articular calcaneal fractures (DIACFs) is lacking. Furthermore, there is a paucity of research comparing complication rates between the two protocols in the aftertreatment phase of DIACFs. Consequently, the safety of EWB following surgery in patients with DIACFs remains uncertain.

In postoperative fracture management, it is well-established that both over- and underloading can hinder recovery. As depicted in Fig. 1, it is hypothesized that maintaining a balance between a certain level of weight bearing and periods of partial inactivity is crucial for successful rehabilitation of trauma patients [12]. Therefore, the goal of aftertreatment in operatively treated trauma patients should be to prevent issues stemming from exceeding the upper and/or lower thresholds of weight bearing (i.e., overloading and immobilization). Literature confirms that inadequate loading may result in complications such as persistent edema, osteoporosis due to inactivity, reduction in joint mobility, muscle strength, functional capacity, and connective tissue load-bearing capacity [13]. Conversely, excessive loading can lead to failure of osteosynthesis and migration of fracture parts, subsequently resulting in malunion or nonunion [14]. Simultaneously, a certain minimum level of loading is necessary to induce micromovements between fractured bone components and initiate biological processes that facilitate fracture healing and counteract the effects of immobilization, such as muscle mass loss [15].

**Fig. 1 Fig1:**
[figure not shown]
Schematic overview of the consequences of loading on the consolidation

Currently, the AO (*Arbeitsgemeinschaft für Osteosynthesefragen*) protocol for postoperative management of DIACFs involves NWB for 8 to 12 weeks, followed by a weekly 25% increment in weight loading [16]. Despite the well-established positive impact of early weight bearing on fracture healing and preservation of muscle and bone mass, this regimen has remained the standard for decades [17]. Consequently, there arises a question as to whether physicians and physiotherapists may be overly cautious, driven by concerns about secondary fracture displacement or mechanical construct failure.

### Objectives {7}

The purpose of ‘the PIONEER study’ is to conduct a randomized controlled trial in surgically treated patients with DIACFs who undergo rehabilitation with either PWB or Restricted Weight Bearing (RWB). The primary aim of the study is to explore functional outcomes for surgically treated patients with DIACFs and will be allocated to one of the two distinct rehabilitation protocols (PWB or RWB) over a 6-month period. Secondary objectives include comparing disparities in additional functional outcomes and health-related quality of life (HRQoL). Additionally, variances in radiographical parameters (Böhlers angle and posterior facet joint alignment), cost-effectiveness, and complication rates will be assessed and compared.

### Trial design {8}

The PIONEER study will be a prospective multicenter RCT conducted in the Netherlands, with parallel groups, allocation ratio 1:1. The primary outcome measure will be evaluated based on the principles of non-inferiority. Secondary outcomes on superiority.

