#### Secondary outcomes

Secondary outcomes encompass several measures.The Maryland Foot Score (MFS): The MFS is a tool for assessing foot disorders, comprising evaluations of pain, gait, functional activities, and cosmesis. Scores range from 0 to 100 points, with < 50 indicating poor, 50–74 as fair, 75–89 as good, and 90–100 as excellent outcomes [22]. Time points: collected at 2 weeks, 6 weeks, 12 weeks, and 6 months post-surgery.Health-related quality of life (HRQoL) using the EuroQoL 5-Dimension 5-Level (EQ-5D-5L): This self-administered questionnaire comprises five dimensions (mobility, self-care, daily activities, pain/discomfort, and depression/anxiety), each rated on five levels. Utilities calculated using preferences from the Dutch tariff will enable Quality Adjusted Life Years (QALY) scoring, besides the questionnaire is recommended by the Dutch guidelines [23, 24]. Time points: collected at baseline, 2 weeks, 6 weeks, 12 weeks, and 6 months post-surgery.Radiographical characteristics: Evaluation of Böhlers angle and posterior facet joint alignment via radiographic assessment by a blinded radiologist will be conducted at scheduled physician visits. CT scans early post-operatively and at 6 months will be used to measure differences in Böhlers angle and posterior joint alignment [25]. Differences in the Böhlers angle and posterior joint alignment (Δ = CT_6months_—CT_post-op._) will be calculated. Normal Böhlers angle ranges between 25° and 40° [26]. Intra-articular step-off or gap < 2 mm of the posterior facet is considered well-reduced [3]. Time points: early post-operative (‘baseline’) and at 6 months post-surgery CT scan.Medical consumption and productivity: Measured using the Medical Consumption Questionnaire (iMCQ) and Productivity Costs Questionnaire (iPCQ). The iMCQ assess healthcare utilization, while the iPCQ captures productivity losses. The iPCQ and iMCQ are generic and complimentary questionnaires, that can be used in every indication and are adapted to the context of this study [27]. Time points: collected at baseline, 12 weeks, and 6 months post-surgery.Total complication rate: A wound infection is defined as (but not limited to) purulent wound drainage, inflammation, erythema, fever, increased white blood cell count, increased C-reactive protein and/or increased erythrocyte sedimentation rate, necessitating admission for antibiotic treatment and/or revision surgery for infection.A dislocation is defined as the migration of fracture parts, defined as >3 mm articular step-off or gap and/or varus/valgus malalignment > 5° after weight bearing. A non-union is defined as no radiographic union achieved after 6 months or no progress in healing. Failure of osteosynthesis is defined as loosening or breakage of implants, including the rate of reoperation (e.g., leading to removal of material, arthrodesis). Postoperative arthritis will be screened on CT scans. Time points: evaluated at 2 weeks, 6 weeks, 12 weeks, and 6 months post-surgery.

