### Sample size {14}

To our knowledge, there is no literature available that directly compared our primary outcome (AOFAS Score) in PWB versus RWB for surgically treated patients with DIACFs. Therefore, unfortunately, the MCID is unknown for the AOFAS Score [28, 29].

However, the estimated minimal clinical difference (MCID) can be calculated as one half of the standard deviation (0.5 SD) [30]. Preliminary results of a systematic review that is currently performed by our group, found a mean AOFAS Score of 83.7 (SD 8.5) for the RWB group. 0.5 × 8.5 results in a MCID of 4.3, respectively.

Besides, a recent Cochrane review reported a MCID for the AOFAS Score in other foot conditions that range from 2.0 to 7.9 [29]. This results in a mean MCID of (2.0 + 7.9)/2 = 5, respectively.

For this sample size calculation, a MCID of 5 points was assumed, approximating a 0.5 SD of the estimated mean AOFAS score after RWB for surgically treated patients with DIACFs [30].

In order to be able to detect such a difference between the two groups, assuming that an equal number of patients in both groups will be included, with an alpha of 5% and beta of 20% (power 80%), a pooled SD of 8.5 and a true difference of zero points between the RWB and PWB group the sample size should be at least 46 for both groups = 92 in total. Anticipating a 20% drop out a total of 115 patients must be recruited for this study. The sample size calculation was performed with a two-sample mean test for non-inferiority using the TrialSize package within “R.”

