## Statistical methods

### Statistical methods for primary and secondary outcomes {20a}

Baseline patient characteristics will be presented according to the by aftertreatment regime. Continuous variables will be summarized using either mean and standard deviation or as median and interquartile range. Categorical variables will be summarized as count and percentages.

All analyses of the primary and secondary study parameters will be conducted following both the intention-to-treat principle and the per-protocol principle. Statistical significance will be determined using a *p*-value of ≤ 0.05. All analyses will be carried out using “R” or IBM SPSS version 28 or later.

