#### Secondary study parameters

The MFS score at 6 months will be analyzed using a linear regression model to compare between the PWB and RWB groups, similar to the analysis of the primary study parameter. EQ-5D scores at 6 months will be compared between groups using a linear mixed-effects regression model to account for clustering of multiple observations within each patient. Both absolute differences between groups, as well as the difference in slope over time will be estimated. All parameters will be reported, including 95% confidence interval. Binary secondary outcome variables (i.e., having received any secondary surgical procedure, experienced any type of complication, showing differences on radiographs) will be compared between groups using logistic regression analysis.

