## Discussion

The current paper outlines the protocol for a multicenter randomized controlled trial to be conducted in 11 hospitals across the Netherlands. It provides comprehensive details on the study’s objectives, methodology, including patient flow, randomization procedures, recruitment strategies, rehabilitation protocols, and data analysis methods. Additionally, it offers guidance for presenting and publishing the results. Notably, this study will be the first to establish an optimal rehabilitation regimen for patients with DIACFs, and it possesses several strengths. Firstly, it adopts a randomized controlled trial design, widely regarded as the gold standard in clinical research. The involvement of multiple Dutch hospitals enhances the generalizability of the findings. Moreover, this design minimizes potential biases inherent in observational studies, facilitating a more accurate assessment of intervention effectiveness.

However, several limitations should be acknowledged. Firstly, the inevitable heterogeneity in surgical treatment across participating centers may impact protocol consistency and consequently, outcomes. Standardized protocols and staff training will address this concern. Secondly, compliance bias may arise as patients may not strictly adhere to allocated weight bearing regimes. Again, standardized protocols and staff training will mitigate this bias. Thirdly, patient blinding is unfeasible for rehabilitation, potentially compromising methodological rigor and introducing bias into results. However, blinding will be implemented for radiological evaluations. Additionally, the 1-year follow-up period limits assessment of longer-term outcomes, although the greatest effect of early weight bearing is typically observed within the first 3 to 6 months post-surgery.

In conclusion, existing retrospective literature provides inadequate methodological data to determine the superiority of one rehabilitation protocol over another. The PIONEER study will offer evidence on whether to favor one weight bearing protocol over another and will ascertain the safety and efficacy of these protocols for patients with DIACFs.

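### Complications are tested for superiority in a trial sized only for AOFAS, so a non-significant result cannot support the promise to ascertain safety

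*Protocol article*

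**What the plan says.** - **Open question.** Background and rationale {6a} says that "the safety of EWB following surgery in patients with DIACFs remains uncertain".
- **Framework.** Trial design {8}: "The primary outcome measure will be evaluated based on the principles of non-inferiority". The next sentence covers everything else: "Secondary outcomes on superiority". No exception is made for harms.
- **Outcome.** Secondary outcomes lists the complication composite, beginning "Total complication rate: A wound infection is defined as (but not limited to) purulent wound drainage". It goes on to dislocation, non-union, failure of osteosynthesis with reoperation, and arthritis screened on CT.
- **Method.** Secondary study parameters says that binary outcomes, including any complication, "will be compared between groups using logistic regression analysis". The general rule in Statistical methods {20a} is: "Statistical significance will be determined using a *p*-value of ≤ 0.05".
- **Size.** Sample size {14} uses AOFAS only, "with an alpha of 5% and beta of 20% (power 80%), a pooled SD of 8.5 and a true difference of zero points". This gives 46 per arm, 92 in total, and 115 after 20% dropout. No complication rate or tolerable excess enters it.
- **Promised conclusion.** The Discussion closes by saying that the study "will ascertain the safety and efficacy of these protocols for patients with DIACFs".

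**The concern.** A superiority test can show that two arms differ on a harm. If it does not reject, it has not shown that they are alike, and in a small trial non-rejection can be the likely result even when a real excess exists. The plan accepts this logic for AOFAS, where it sets a margin of 5 points and reads the confidence limit against it. For the outcome that carries the safety claim it sets the opposite framework, with no tolerable excess and no absolute measure of the difference.

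At stake is how the main result will be read. Non-inferior AOFAS together with no significant difference in complications would invite the conclusion that early loading is safe, and the Discussion has already promised a conclusion of that kind. Under the stated analysis, that result could also arise with a material excess of complications.

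**Working it through.** **1. Reproduce the plan's own figure.** Inputs from Sample size {14} and Primary study parameter: margin 5, SD 8.5, true difference 0, power 80%, and a two-sided 5% test, so 2.5% in the relevant tail.

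n per arm = 2 × [8.5 × (1.960 + 0.842) / 5]² = 45.4, rounded up to 46. Total 92; 92 / 0.80 = 115. The stated figures reproduce. (With 5% in one tail the result would be 36 per arm, which does not match.)

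**2. Per-arm sizes for complications.** 46 if only the planned evaluable patients contribute, and about 57 if all 115 do (115 / 2 = 57.5).

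**3. Assumptions.** The documents give no complication rate, so RWB rates from 5% to 25% are assumed. The 5% level is taken as two-sided. An unadjusted comparison of two proportions stands in for the logistic regression.

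**4. Power to detect a doubling.** With rates p₁ and p₂ = 2p₁, and p̄ their mean:

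power = Φ{ [ |p₂ − p₁| − 1.96 √(2p̄(1 − p̄)/n) ] / √[(p₁(1 − p₁) + p₂(1 − p₂))/n] }

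For 10% versus 20% and n = 46: √(2 × 0.15 × 0.85 / 46) = 0.0745, and 1.96 × 0.0745 = 0.146. The denominator is √[(0.09 + 0.16)/46] = 0.0737. Then (0.100 − 0.146)/0.0737 = −0.62, so power is 26.7% and the doubling is missed 73% of the time. With n = 57, power is 31.9% and it is missed 68% of the time.

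**5. Precision when the rates are equal.** Half-width of the 95% interval for the risk difference = 1.96 √(2p(1 − p)/n). At 10%: 1.96 √(0.18/46) = 12.3 points and 1.96 √(0.18/57) = 11.0 points.

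| Assumed RWB rate, doubled in PWB | Power, 46 / 57 per arm | Doubling missed, 46 / 57 | Half-width at equal rates (points), 46 / 57 | n per arm for 80% power |
|---|---|---|---|---|
| 5% to 10% | 14.6% / 17.1% | 85% / 83% | 8.9 / 8.0 | 435 |
| 10% to 20% | 26.7% / 31.9% | 73% / 68% | 12.3 / 11.0 | 199 |
| 15% to 30% | 40.5% / 48.3% | 60% / 52% | 14.6 / 13.1 | 121 |
| 20% to 40% | 55.4% / 64.8% | 45% / 35% | 16.3 / 14.7 | 82 |
| 25% to 50% | 70.4% / 79.5% | 30% / 21% | 17.7 / 15.9 | 58 |

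**6. Check without the normal approximation.** For 10% versus 20%, exact enumeration gives power of 28% / 32% for the chi-square test and 18% / 23% for Fisher's test.

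**7. When would a doubling be excluded?** With equal observed rates p, a doubling is an excess of p. Setting the half-width equal to p gives p = 7.68 / (n + 7.68), where 7.68 = 2 × 1.96². That is 14.3% for n = 46 and 11.9% for n = 57. Below these rates the interval would still include a doubling; above them it would not.

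**The case against.** The strongest reply is that nothing in the plan states a wrong decision rule. Objectives {7} says only that complication rates will be assessed and compared, no power is claimed for them, and the safety promise is a closing sentence in the Discussion. Low power for a secondary harm outcome is common and is not in itself an error. Safety is also not left to one p-value. Secondary study parameters mentions 95% confidence intervals, a blinded radiologist reads the change in alignment on CT, the study team reviews safety data about quarterly, and adverse events are reported.

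Much of this stands, and it limits the point. Four stronger readings are tempting but not supported:

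- **That the trial would miss a doubling about 70% of the time.** This holds only near an assumed RWB rate of 10% to 12%. The composite is broad, and nothing in the documents favours that rate. At 20% or more a doubling is more likely to be detected than missed.
- **That a doubling could not be excluded.** With equal observed rates this fails above about 12% to 14% (step 7).
- **That the superiority test is the only safety provision.** The items listed above show otherwise. The sentence on confidence intervals comes just before the one on binary outcomes, so it may also cover the odds ratios. Such an interval would still be relative and would not show the absolute excess that remains possible.
- **That the sample size is wrong.** It reproduces exactly for its stated purpose.

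The reply does not remove the mismatch between a superiority framework fixed for all secondary outcomes and a stated safety conclusion. Both are in the text, so this is not a detail left to an unseen analysis plan.

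**Conclusion.** The point holds in a limited form. The plan promises to ascertain safety, but the comparison it prescribes for complications cannot deliver that through a non-significant result. This is a matter of logic and does not depend on the complication rate.

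The practical size does depend on the rate, which the documents do not give. For assumed RWB rates up to 15%, a doubling would be missed more often than not (52% to 85%). At 20% it would be missed 45% or 35% of the time, and at 25% 30% or 21%. Equal rates between 5% and 20% would leave excesses of about 8 to 16 points compatible with the data. These figures assume 46 to 57 patients per arm and an unadjusted two-sided 5% comparison. The approximation is rough at the lowest rate, where 46 × 0.05 gives only about two expected events in an arm.

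No change to the sample size or to data collection follows from this. It is an inexpensive correction that should be made, because it changes what the trial may conclude.

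**What to change.** 1. **Trial design {8}:** state that complications, including displacement, are exempt from the superiority framing and will be estimated.
2. **Secondary study parameters:** beside the logistic regression, add the absolute risk difference (PWB minus RWB) with its 95% confidence interval. State that any safety statement will rest on the upper limit of that interval, and that a non-significant difference will not be read as evidence of safety.
3. **Discussion:** replace the promise to ascertain safety with wording such as *will estimate complication rates and their difference with 95% confidence intervals*.

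Do not write an assumed complication rate, or a detectable limit derived from one, into the protocol, since the documents give no source for either.

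The cost is one extra estimate from data already collected and a stated claim that is less favourable. No additional patients, visits or measurements are needed.
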